### Recruitment and enrolment

Recruitment was planned to start in April 2024, and the anticipated completion of recruitment (i.e., when the last patient is expected to be enrolled in the trial) is at the end of December 2025. The first patient was successfully recruited on 8 November 2024. To create a well-defined and homogeneous study population, and enhance internal validity, while ensuring participant safety, the following inclusion and exclusion criteria were applied:

#### Inclusion criteria

Minimum age is 18 years.Patients undergoing their first elective aortocoronary bypass surgery (CABG, without valve) with or without the use of a heart-lung machine (extracorporeal circulation).Median sternotomy.Sufficient knowledge of the German language.Adequate cognitive fitness to provide consent for study participation.Valid email address.Regular access to a computer with an internet connection.Participants can provide informed consent at least 5–21 days before the surgery.

#### Exclusion criteria

Emergency surgery.Minimally invasive surgical procedure.Presence of another (non-cardiac) life-threatening condition.Comorbid medical/psychiatric condition causing at least a similar impairment compared with coronary and valvular heart disease.Participation in other interventional/experimental research programmes.

### Procedure

The medical team at the Departments of Cardiac and Thoracic Vascular Surgery informs patients about the study as soon as their surgery is scheduled and they are confirmed to meet the key inclusion criteria—ideally between 21 and 5 days before their surgery. In addition to a brief phone call providing initial information, patients receive a brochure enclosed with their surgery confirmation letter. The brochure outlines the study’s objectives, procedures, duration and includes a link and QR code to the study website. On the website, patients complete anonymous screening questions to determine eligibility (eg, type of surgery, timing and whether it is their first heart surgery). Eligible patients are redirected to the detailed study information and informed consent page. Ineligible patients receive a message informing them they do not qualify for the study and continue to receive only the SOC without being provided any additional study-specific materials or guidance. All screening data—regardless of eligibility—are securely stored in the study database, with personal identifiers removed or coded in accordance with clinical data confidentiality standards.

#### Informed consent

On the informed consent page, patients receive comprehensive information about the study and participation conditions. They can express interest and request more information by providing contact details before giving written consent by ticking a box. Once initial consent is given, a study therapist contacts them by telephone to conduct a more detailed screening; during this call, patients are again informed about the study’s potential risks, have the opportunity to ask additional questions before giving full informed consent and being formally enrolled. During the phone call, the voluntary nature of participation and the option to withdraw at any time are emphasised. The risks of blood sampling are reiterated, and any remaining questions are clarified. As part of routine clinical care, patients are required to provide blood samples prior to surgery; participation in the optional research blood sampling component is voluntary, and patients may still enrol in the study even if they decline to provide study-specific specimens. If patients consent, the presence of relevant mental disorders is assessed using the International Diagnosis Checklists for ICD-10 and the Structured Clinical Interview for DSM-IV^21^ and any incidental findings are communicated to the study team. Patients may choose to be informed of suspected diagnoses, although the study does not expedite psychotherapy access; instead, general guidance on seeking care is provided, without a formal referral pathway. In urgent cases (eg, critical PHQ-9 scores), patients are contacted directly, if possible, in collaboration with the clinic, to ensure immediate support. Medical consent for heart surgery follows the clinic’s protocol.

### Randomisation

After baseline assessment, patients are randomised in a 2:2:1 ratio to the treatment groups (iEXPECT enhanced: iEXPECT limited: SOC) using permuted block randomisation, stratified by baseline disease-related impairment (Pain Disability Index (PDI), <23 or ≥23).^22^

Randomisation is conducted online via REDCap (https://www.project-redcap.org/), a secure web platform for managing online databases and surveys, on the servers of the Coordinating Centre for Clinical Trials (KKS), Philipps-University Marburg. A biometrician from the KKS, who had no involvement in trial analysis or data collection, developed the randomisation script using RStudio V.2022.12.0, and the KKS Data Management Department used this code to generate the final randomisation list. It is not planned to use back-up envelopes. Study therapists log into REDCap, verify that all relevant data (eg, informed consent, inclusion/exclusion criteria, baseline PDI value) are available for each patient, and initiate automated randomisation. Following randomisation, study therapists will grant participants access to the respective online intervention. The experimental groups can immediately begin the intervention. Participants are not explicitly instructed to conceal their group allocation from the treating medical team. However, the medical staff will not receive any information about the group a patient is allocated to and, therefore, be blind regarding group assignments.

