**Trial registration number:**

DRKS00033284.

Strengths and limitations of this studyInvolving three diverse clinical centres enhances generalisability and feasibility assessment across different hospital settings.Use of stratified, permuted block randomisation via REDCap, a secure platform for managing online databases and surveys, ensures allocation concealment and minimises selection bias.Medical staff (caregiver, treating physician) remain blinded to group assignment, reducing the risk of biased treatment effects.Although previous patient feedback informed intervention development, there was no structured patient involvement in designing the current trial.Digital intervention format excludes patients without internet access or sufficient digital literacy, potentially limiting inclusivity.

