### Secondary outcomes

Secondary outcomes include multimodal assessments (ie, self-ratings, expert ratings, clinical facts, biological measures) that were selected to capture a comprehensive picture of psychological, behavioural and clinical processes that may be affected by the intervention and are relevant for evaluating its broader impact and future Phase III trial feasibility. These include measures of preoperative anxiety and need for information (APAIS, Amsterdam preoperative anxiety and information scale),^28 29^ general anxiety and depression (PHQ9, patient health questionnaire; and GAD-7, generalized anxiety disorder scale),^30 31^ and treatment expectations (TEX-Q, treatment expectation questionnaire; and GEEE, generic rating scale for previous treatment experiences),^32 33^ all of which are known to influence surgical outcomes and psychological readiness. We also included constructs such as attitudes towards internet-based interventions (APOI, attitudes towards psychological online interventions),^34^ subjective illness beliefs (B-IPQ, brief-illness-perception questionnaire),^35^ social support (ESSI-D, enriched social support inventory-deutsch)^36^ and trait optimism (LOT-R, revised life orientation test),^37^ which may moderate treatment engagement and response. Furthermore, indicators of digital health literacy (GR-eHEALS, revised German eHealth literacy scale),^38^ physical activity (IPAQ, international physical activity questionnaire),^39^ perceived stress (PSS, perceived stress scale),^40 41^ illness-related disability caused by the current medical condition (PDI, pain disability index adapted version),^22^ pain (VAS, visual analogue scale, 0–10), quality of life (SF-12, short-form health survey)^42^ and treatment satisfaction (ie, rating of fulfilment/violation of pretreatment expectations at the end of the trial) may provide a multidimensional view of patient functioning across time. To explore potential adverse effects and unmet needs, we assess negative side effects (NEQ, negative effects questionnaire)^43^ and prior pretreatment experiences. The following clinical parameters are also included to explore associations between psychological factors and physical recovery: rehospitalisation; length of stay; length of time at intensive care unit; planned and realised surgery; EURO-Score II, European system for cardiac operative risk evaluation^44^; CSS score, Canadian Cardiovascular Society^45^; blood pressure; LVEF, left ventricular ejection fraction; New York heart association (NYHA) score; complications; inflammatory processes (C reactive protein (CRP), IL-6, Interleukin-6, IL-8, Interleukin-8); HRV, heart-rate-variability (ie, triangular index).

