
### Assessment

Assessments take place 5–21 days before the surgery (baseline, T0), preoperatively on the day of hospital admission after the psychological intervention (T1), 7 days after surgery (T2) and 6 months after surgery (T3) (for an overview, see figure 2). Psychological data will be collected through questionnaires (eg, regarding disease-related impairment, quality of life, depression and anxiety) and takes place online via the secure web-based survey platform UniPark (https://www.unipark.com/). At each assessment point (T0–T3), completion of the psychological questionnaires will require approximately 30 min. Participants are encouraged to complete them online via UniPark, although paper-based versions may be provided by clinical staff in cases of technical difficulties, and retention is supported through personalised email invitations, reminder emails and phone calls. These strategies have been shown to enhance compliance and reduce attrition,^46^ helping to ensure complete data collection across all time points. Patients will be asked to complete the questionnaires and to contact study therapists if they have any questions. For a detailed overview, see the online supplemental table S2, which shows the applied questionnaires, biological parameters and case report forms (CRFs). Furthermore, semistructured interviews with a small subset of CABG patients (up to N=12) will be conducted on a voluntary basis after surgery to retrospectively explore preparation needs and qualitatively assess the intervention. Interviews (30–45 min) will be audio-recorded, transcribed and analysed using qualitative content analysis.^47^ All data will be anonymised.

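### Staff blinding is listed as a strength that reduces bias, but it is unprotected against disclosure by patients and no check on it is described

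*Protocol article*

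**What the plan says.** The strengths and limitations box of the protocol article states: "Medical staff (caregiver, treating physician) remain blinded to group assignment, reducing the risk of biased treatment effects".

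The Randomisation section gives the procedure behind that claim. Study therapists start the allocation in REDCap and then open the intervention: "Following randomisation, study therapists will grant participants access to the respective online intervention". On concealment by patients it says: "Participants are not explicitly instructed to conceal their group allocation from the treating medical team". It then draws its conclusion: "the medical staff will not receive any information about the group a patient is allocated to and, therefore, be blind regarding group assignments".

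The Secondary outcomes section lists, among the clinical parameters, "rehospitalisation; length of stay; length of time at intensive care unit". The Data analysis plan says that secondary outcomes will be described and used to guide power calculations for a Phase III trial.

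**The concern.** The conclusion in the Randomisation section does not follow from its premise. Withholding the allocation closes the route from the study to the staff. It does nothing about the route from the patient to the staff, and the same paragraph says that patients are not asked to keep their arm private. The strengths box then presents the conclusion without the caveat and adds that bias is reduced.

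If staff learn the arm, and if discharge or intensive care decisions respond to that knowledge, arm differences in length of stay or intensive care time could partly reflect staff behaviour. The trial report would still describe staff as blinded, and no data would exist to test that description. The Introduction cites shorter hospitalisation as a benefit of the face-to-face version, so length of stay may well matter in the later trial. A feasibility trial is the natural place to learn whether staff blinding can be kept.

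**Working it through.** The point rests on no sample size, rate or error level, so there is nothing to calculate. The check sets the statements side by side.

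1. **Claim.** The strengths box says that caregivers and treating physicians stay blinded and that this lowers bias. There is no qualifier.

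2. **Stated mechanism.** The Randomisation section offers one: staff are given no allocation information. The study therapists, not the ward, randomise and open access. This supports the statement that staff are not informed by the study.

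3. **What the mechanism leaves open.** Patients know whether they received online modules and whether guidance came by phone or email. They are not asked to conceal this.

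4. **Is disclosure plausible?** Under Procedure, the medical team itself introduces the study, so staff know that it exists. Table 1 shows that the modules give patients a personalised recovery plan, a health-behaviour plan and preparation for intensive care and incision pain. These are subjects that a patient could raise on the ward. According to the Assessment section, T1 falls on the day of admission, after the intervention, so hospital contact follows directly. This shows that disclosure is possible and natural. It gives no rate.

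5. **Is there a check?** The article describes no question to staff, record or other measure of whether the arm became known.

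6. **What could be affected?**
   - Recruitment and retention, module completion and acceptance do not depend on ratings by ward staff. They are unaffected.
   - Length of stay and intensive care time can be influenced by staff decisions. This is an assumption about ordinary hospital practice; the article does not say how they are decided.
   - These outcomes are analysed descriptively, and the Sample size section says that the trial is not designed to detect group differences. No confirmatory result depends on them. Their stated further use is in Phase III planning.

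Steps 1 to 3 give the result: the text supports non-disclosure by the study, and the strengths box claims more than that.

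**The case against.** The best defence is that the protocol is open about the missing instruction and that blinding does have real protection. Allocation is handled by study therapists in REDCap. The modules are done at home and guidance is remote. Modules 1 to 3 at least should be finished no later than the day before surgery, and boosters come at 6, 12 and 18 weeks. Little or no intervention activity is therefore scheduled during the postoperative stay. The outcomes at issue are descriptive, and a request introduced partway through recruitment would leave a mix of patients with and without it.

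Most of this stands, and it keeps the point small. It does not rescue the wording. The open admission appears in the Randomisation section and does not reach the strengths box, and remote delivery does not stop a patient from talking.

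Some stronger readings are tempting, but the document does not support them:

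- **That blinding fails.** The text shows an unprotected route. It does not show that anyone uses it.
- **That questionnaires reveal the arm.** A reader might combine the provision that "paper-based versions may be provided by clinical staff in cases of technical difficulties" with the satisfaction questionnaire (CSQ-I) due at T1, and infer that the paper pack gives the allocation away. Data collection normally "takes place online via the secure web-based survey platform UniPark", and paper is only a fallback. The article does not say that paper sets differ by arm or that staff read them, and supplemental table S2 is not shown.
- **That staff grade NYHA class or angina while knowing the arm.** These measures are listed without a rater or a timepoint.

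**Conclusion.** The point holds in a limited form. Staff are not told the arm by the study, but blinding is not secured against disclosure by patients, and no check on it is described. The unqualified strength statement should be toned down.

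The size of any bias cannot be estimated, because neither the frequency of disclosure nor its effect on staff decisions is given. A reader might take the planned allocation, 64 + 64 = 128 intervention patients out of 160 (80%), as the share who could unblind staff. That is an allocation count and not a disclosure rate. It also omits the 32 standard-care patients, who could disclose their arm just as easily.

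The sample size and the three primary criteria are unaffected. The conclusion assumes that staff decisions can influence length of stay and intensive care time, and that the full protocol contains no safeguard beyond those in the article. It is a cheap improvement of minor priority.

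**What to change.** 1. Reword the strengths box and the end of the Randomisation paragraph to say that staff are not informed of allocation and that disclosure by patients is possible. This costs nothing and can be done at any stage of recruitment.

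2. For patients still to be enrolled or admitted, add one line to the study invitation or the T1 reminder asking them not to mention their group to ward or surgical staff unless it is needed for their care.

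3. Add one yes/no eCRF item at discharge on whether staff learned the arm. Report it by arm beside length of stay and intensive care time, so that whoever plans the Phase III trial can judge those figures.

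The cost is a sentence in the patient materials, one eCRF item and a notification to both ethics committees. Patients already treated will not have had the instruction, so the report should say when it was introduced. Randomisation, intervention and sample size do not change.

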### iEXPECT intervention

Participants in the intervention groups receive an email invitation with their patient IDs to access the online study platform (https://www.minddistrict.com/de-de) and instructions for use. They can progress through the intervention modules and contact the study team with questions.

The internet-based iEXPECT intervention with four modules before, and three guided booster sessions after surgery can be done from home in the participants’ own time (for an overview, please see the intervention schedule in figure 2). Participants receive semistructured guidance via email or phone (~10-15 min) within 1–2 working days after each module, reinforcing strategies and addressing challenges. Noteworthy, patients in the iEXPECT enhanced group will receive more tailored guidance as the personal contact via telephone allows study therapists to directly interact with the patients to ensure patients’ complete understanding. Furthermore, a second placebo mechanism (besides expectations) is used: positive interaction between patient and therapist.^23^

**Figure 2 F2:**
[figure not shown]
Intervention schedule for participants receiving the iEXPECT intervention. Days (**d**); weeks (**w**); months (**m**). Guidance consists of feedback on the previous module and is provided through email (iEXPECT limited) or a short phone call (~10-15 min; iEXPECT enhanced), within 1–2 working days after finishing each module. Modules 1–4 enforce positive and realistic expectations while addressing and correcting dysfunctional expectations and illness beliefs. Boosters recap key topics from the previous modules to sustain personal control expectations postoperatively. CABG, coronary artery bypass graft; iEXPECT, expectation manipulation online intervention.

In the iHEART trial, the number of booster sessions is increased based on PSY-HEART-I findings, which showed that the ‘EXPECT’ interventions raised preoperative personal control expectations but patients struggled to maintain them postoperatively.^24^ The iEXPECT modules incorporate persuasive design elements^25 26^ to improve adherence. Examples of these elements include primary task support, such as exercises and homework; dialogue support, including calendars for upcoming modules and reminder emails or phone calls, depending on the experimental group a patient is in; and system credibility support, demonstrated through the inclusion of information sources and the logos of universities and clinics.

## Outcomes

### Primary outcomes

The primary outcomes of the iHEART trial are focused on evaluating the feasibility and acceptance of the iEXPECT intervention and the study design.

#### Feasibility

Feasibility is defined across two dimensions, namely (1) feasibility of the study design, referring to the successful recruitment and retention of participants across multiple study sites (outcome criterion 1) and (2) feasibility of intervention implementation, referring to the patients’ engagement with the iEXPECT modules prior to surgery (outcome criterion 2). These outcomes reflect whether the trial can be operationalised as intended and whether participants are willing and able to engage with the digital intervention components.

#### Acceptance

Acceptance is defined as participants’ subjective evaluation of the iEXPECT intervention (outcome criterion 3). This includes perceived enjoyableness, usefulness and the intervention’s relevance to their daily social functioning. Ratings are gathered through self-report at the end of each module and via a standardised satisfaction questionnaire (CSQ-I)^27^ after intervention completion (T1) and at 6-month follow-up (T3). Together, these outcomes will inform the practicality and perceived value of the intervention from the patient’s perspective and provide critical insight for the planning of a future full-scale efficacy trial.

### Secondary outcomes

Secondary outcomes include multimodal assessments (ie, self-ratings, expert ratings, clinical facts, biological measures) that were selected to capture a comprehensive picture of psychological, behavioural and clinical processes that may be affected by the intervention and are relevant for evaluating its broader impact and future Phase III trial feasibility. These include measures of preoperative anxiety and need for information (APAIS, Amsterdam preoperative anxiety and information scale),^28 29^ general anxiety and depression (PHQ9, patient health questionnaire; and GAD-7, generalized anxiety disorder scale),^30 31^ and treatment expectations (TEX-Q, treatment expectation questionnaire; and GEEE, generic rating scale for previous treatment experiences),^32 33^ all of which are known to influence surgical outcomes and psychological readiness. We also included constructs such as attitudes towards internet-based interventions (APOI, attitudes towards psychological online interventions),^34^ subjective illness beliefs (B-IPQ, brief-illness-perception questionnaire),^35^ social support (ESSI-D, enriched social support inventory-deutsch)^36^ and trait optimism (LOT-R, revised life orientation test),^37^ which may moderate treatment engagement and response. Furthermore, indicators of digital health literacy (GR-eHEALS, revised German eHealth literacy scale),^38^ physical activity (IPAQ, international physical activity questionnaire),^39^ perceived stress (PSS, perceived stress scale),^40 41^ illness-related disability caused by the current medical condition (PDI, pain disability index adapted version),^22^ pain (VAS, visual analogue scale, 0–10), quality of life (SF-12, short-form health survey)^42^ and treatment satisfaction (ie, rating of fulfilment/violation of pretreatment expectations at the end of the trial) may provide a multidimensional view of patient functioning across time. To explore potential adverse effects and unmet needs, we assess negative side effects (NEQ, negative effects questionnaire)^43^ and prior pretreatment experiences. The following clinical parameters are also included to explore associations between psychological factors and physical recovery: rehospitalisation; length of stay; length of time at intensive care unit; planned and realised surgery; EURO-Score II, European system for cardiac operative risk evaluation^44^; CSS score, Canadian Cardiovascular Society^45^; blood pressure; LVEF, left ventricular ejection fraction; New York heart association (NYHA) score; complications; inflammatory processes (C reactive protein (CRP), IL-6, Interleukin-6, IL-8, Interleukin-8); HRV, heart-rate-variability (ie, triangular index).
